#### **Diagnosis, symptoms and signs**

If a diagnosis is already available, the diagnosis should be recorded on the eCRF rather than the individual signs and symptoms (e.g., liver failure should be recorded rather than jaundice, elevated transaminases, and asterixis). If signs and symptoms cannot be ascertained to be caused by the diagnosis at the time of reporting, they will be recorded as a separate AE/SAE. If it is determined that the signs and symptoms are caused by the diagnosis, only the diagnosis is reported separately and the symptoms and signs are included in the diagnosis. AE needs to delete the record of symptoms and signs, and SAE needs to send a follow-up update report.

#### **Adverse Events Secondary to Other Events**

In general, adverse events secondary to other events (e.g., caused by other events or

clinical sequelae) should be recorded as the primary event, unless the secondary event is serious or serious. However, secondary events with significant clinical significance should be recorded as separate adverse events in the eCRF if they occur at a different time from the primary event. If the relationship between the events is unclear, they should be recorded separately in the eCRF.

### **Persistent or Recurrent Adverse Events**

A persistent adverse event is an adverse event that persists without resolution between the subject's two evaluation time points.

A recurrent adverse event is an adverse event that has resolved between the two evaluation time points but occurs later. The occurrence of the event should be recorded separately in the eCRF.

### **Laboratory test abnormality**

Clinically significant laboratory abnormalities should be reported as AE. It is the responsibility of the investigator to review all laboratory abnormalities and to make medical judgment as to whether each laboratory abnormality should be reported as an AE.

### **Pre-existing medical condition**

The existing symptoms/signs of subjects during the screening period should be recorded and reported as adverse events only when the severity, frequency and nature of the symptoms/signs are aggravated (except for the deterioration of the disease condition under study) after entering the trial. Changes from the previous state such as "increased headache frequency" should be reflected in the recording.

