#### 4.1 Inclusion Criteria

Subjects met all of the following criteria to be included in the study:

1. Age 18 ~ 75 years (both inclusive), male or female;
2. Obese:  $BMI \geq 28.0 \text{ kg/m}^2$ ; Or overweight:  $24 \leq BMI < 28.0 \text{ kg/m}^2$  with at least one of the following manifestations: i. Strong appetite, unbearable hunger before meal, and more food intake per meal; ii. Patients with one or more of pre-diabetes (impaired fasting glucose and/or impaired glucose tolerance), hypertension, dyslipidemia (see Annex 4 for reference standards), and fatty liver (within 6 months prior to screening); iii. Combined weight-bearing joint pain; iv. Obesity-induced dyspnea or obstructive sleep apnea syndrome;
3. Controlled by diet and exercise alone for at least 12 weeks at screening, with body weight change of less than 5%;
4. Able to understand the procedures and methods of this study, willing to strictly comply with the clinical trial protocol to complete this trial, and voluntarily sign the informed consent form.

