## **7 Safety Reporting and Adverse Event Management**

### **7.1 Definition of Adverse Events**

An Adverse Event (AE) is defined as any untoward medical occurrence in a clinical trial subject starting from signing the informed consent form, regardless of whether it is causally related to the study drug, which is judged as an AE, including but not limited to

the following situations:

- Exacerbation of pre-existing (before entering the clinical trial) medical condition/disease (including aggravation of symptoms, signs, laboratory test abnormalities);
- Any newly occurring untoward medical condition (including symptoms, signs, newly diagnosed diseases);
- Abnormal clinically significant laboratory values or results.

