### **7.5.1 Adverse event collection and time interval**

Investigators were informed of adverse events by asking subjects non-inducing questions.

All adverse events, including serious adverse events, whether observed by the investigator or spontaneously reported by the subject, were collected from the time of signing the informed consent form until the end of the study. At the end of the study, if the investigator becomes aware that a subject has experienced a serious adverse event related to the study drug or procedure, the event should still be reported to the sponsor.

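### The rule for pre-existing symptoms in section 7.5.3 is narrower than the adverse event definition in 7.1, conflicts with its own example, and exempts a disease condition it does not define

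*Protocol*

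**What the plan says.** The definition in Protocol 7.1 lists among adverse events: "Exacerbation of pre-existing (before entering the clinical trial) medical condition/disease (including aggravation of symptoms, signs, laboratory test abnormalities". It attaches no further test and exempts no disease. Section 7.5.1 follows the same line for collection: "All adverse events, including serious adverse events, whether observed by the investigator or spontaneously reported by the subject" are to be collected from consent to the end of the study.

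Section 7.5.3, under *Pre-existing medical condition*, sets the rule that a site applies when filling in the form. Existing symptoms and signs are to be entered as adverse events "only when the severity, frequency and nature of the symptoms/signs are aggravated (except for the deterioration of the disease condition under study"; the words in parentheses are its one exception. The paragraph closes by asking that a change from the previous state be visible in the entry, and its example is an increase in how often headaches occur.

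The disease under study is not defined there. Section 4.1 admits subjects with BMI of at least 28. It also admits overweight subjects with BMI from 24 to below 28 who have at least one listed manifestation. One route is "Patients with one or more of pre-diabetes (impaired fasting glucose and/or impaired glucose tolerance), hypertension, dyslipidemia" or fatty liver. The others are strong appetite, weight-bearing joint pain, and obesity-induced dyspnoea or obstructive sleep apnoea.

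Section 2.2.1 makes the incidence of adverse events part of the primary endpoint.

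**The concern.** The section that sites use to decide what to enter is narrower than the section that defines what counts. It narrows in two places: the conjunction, and an exemption whose scope is left open. Two sites, each following the protocol, could treat the same worsening of an existing symptom differently.

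The stake is the primary endpoint. The definition of a serious adverse event in 7.2 and the escalation criterion on severe related events in 3.2.1 also start from an event that has been recognised as adverse. This is a rule for data entry, so no analysis plan can restore an event that was never entered.

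**Working it through.** The protocol gives no figure to reproduce here, so the check compares passages.

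**Step 1: the conjunction.** Three features can each be aggravated or not. The patterns with at least one aggravated number 2³ − 1 = 7.

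| Reading | Patterns recorded |
|---|---|
| 7.1, any exacerbation | 7 of 7 |
| 7.5.3 literally (*only when* all of A, B and C) | 1 of 7 |
| 7.5.3 with *or* | 7 of 7 |

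The patterns are not equally likely, so this is not an estimate of lost events. It shows how far apart the two rules are as written. The headache example is one of the six patterns that the literal rule excludes, so the paragraph contradicts itself as well as 7.1.

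**Step 2: the exemption.** Section 7.1 has none, so the two sections conflict under any reading of the parenthesis. The size of the conflict depends on the reading:

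- *Narrow:* the disease under study is overweight or obesity itself. Little beyond weight gain is exempt, and weight is measured at every scheduled visit (Tables 2, 4 and 6).
- *Broad:* it includes the obesity-related conditions that qualify overweight subjects in 4.1. Worsening of any of them could then be treated as exempt.

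**Step 3: what other rules still capture.** Section 7.5.3, under *Laboratory test abnormality*, makes clinically significant laboratory abnormalities adverse events and has no exemption. Section 6.2.3 does the same for clinically significant vital-sign abnormalities. Glucose, lipids, transaminases and blood pressure are therefore largely covered. What remains open is mainly symptomatic: joint pain, dyspnoea and sleep apnoea under the broad reading, and any existing symptom under the literal three-part test.

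**Step 4: scale.** Section 8.2 plans 8 IBI362 and 4 placebo subjects in each of five cohorts. One subject recorded or not recorded moves the incidence of a term by:

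- IBI362 arm of a cohort: 1/8 = 12.5 percentage points
- placebo arm of a cohort: 1/4 = 25 points
- placebo pooled over five cohorts: 5 × 4 = 20 subjects, 1/20 = 5 points

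Exact (Clopper-Pearson) 95% intervals for 8 subjects are 0 to 36.9% for 0/8, 0.3 to 52.7% for 1/8 and 3.2 to 65.1% for 2/8. They overlap widely, so one entry does not change a statistical conclusion. It does decide whether a term appears in an arm at all.

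The documents do not say how many subjects had existing symptoms that worsened, so the number of events at risk cannot be computed.

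**The case against.** The strongest reply is that 7.5.3 is only loosely worded. It does not say *all three*. Its own example points to *or*, as do 7.1 and 7.5.1, and a sensible site would read it so. The disease under study is most naturally overweight or obesity, as in the study title, the population and the objectives. The comorbidities in 4.1 are alternative entry features for the overweight stratum only. Subjects with BMI of at least 28 need none, and an overweight subject can qualify on appetite alone. Laboratory and vital-sign changes have their own rules, and they are summarised whether or not they are coded as adverse events (8.4.3 and 8.4.5). Section 8.1 plans no formal test on the primary endpoint. Table S1 in the same file lists hypertension, hyperlipidaemia and raised ALT as treatment-emergent events, which gives no sign that such terms were treated as exempt.

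Most of this stands, and it limits the point. A reader might infer that the protocol sets a firm three-part test, or that events have been removed from the primary endpoint. The documents support neither: the example contradicts the strict test, and no missing event is identified. Table S1 settles nothing either way, because it does not say whether the listed events were new or were worsenings of existing conditions.

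The reply does not remove the conflict. The most natural reading of a site rule is not the only one available to a site, and no neighbouring sentence limits the exemption. The laboratory and vital-sign rules do not reach symptoms.

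**Conclusion.** The conflict is real but limited. Section 7.5.3 disagrees with 7.1 on the exemption under any reading. On the conjunction it disagrees with both 7.1 and its own example when read literally. The consequence is possible under-recording of symptomatic worsening in a trial whose primary endpoint includes adverse event incidence. Each affected subject would count for 12.5 points in an IBI362 arm and 25 points in a cohort's placebo arm.

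This rests on two assumptions that the documents neither confirm nor exclude: that some site applies the sentence literally or reads the exemption broadly, and that some subjects have existing symptoms that worsen in only one or two respects or that belong to a qualifying condition.

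A reader might go further and infer that worsening pre-diabetes, hypertension or dyslipidaemia would go unrecorded. The separate rules for laboratory and vital-sign abnormalities largely answer that. The point touches neither the sample size nor any planned comparison.

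**What to change.** In 7.5.3, under *Pre-existing medical condition*, write *severity, frequency or nature*. Delete the parenthesis, or limit it to an increase in body weight. The paragraph then agrees with 7.1 and with its own example, and worsening of joint pain, dyspnoea, sleep apnoea or another existing condition is recorded at every site.

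The cost is one sentence in the protocol and the matching line in the eCRF completion guideline. A few more adverse events may be recorded, in both arms. No other part of the design or analysis changes.

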## **7.6 Expedited Reporting of SAE and Pregnancy**

### **SAE Reporting:**

Since the subject signs the informed consent form, if the subject experiences SAE, the investigator must immediately fill in the Serious Adverse Event Report Form, sign and date it, and immediately report it to the PV Department of the sponsor within 24 hours after the investigator is informed of it: [[contact]](mailto:[contact]). For death and life-threatening serious adverse events, the investigator should urgently follow up the missing information and provide a complete SAE report.

At the end of the study, if the investigator becomes aware that a subject has experienced a serious adverse event related to the study drug or procedure, the event should still be reported to the sponsor.

### **Pregnancy**

All subjects of childbearing potential who participate in the clinical trial must take effective contraceptive measures.

If a female subject becomes pregnant during the clinical trial at the time of drug exposure, the subject will be excluded from the study, and the investigator will report the pregnancy to the sponsor within 24 hours of becoming aware of the pregnancy, and the Pregnancy Report/Follow-up Form for Clinical Trials of Innovent will be completed.

If the partner of a male subject at the time of drug exposure becomes pregnant during the clinical trial, the subject continues the clinical trial, reports the pregnancy to the sponsor ([contact]) and completes the Pregnancy Report/Follow-up Form for Innovent clinical trials within 24 hours of the investigator's knowledge of the pregnancy.

The investigator will continuously monitor the subjects who become pregnant and follow up the pregnancy results until 8 weeks after delivery of the mother, and report the results to the sponsor.

If the pregnancy results in stillbirth, spontaneous abortion, fetal anomaly (any congenital anomaly/birth defect) and induced abortion for medical reasons, it will be considered as SAE and should be reported according to the SAE procedure and time limit.

If a subject also experienced an SAE during the pregnancy, it was to be reported according to the SAE reporting procedure.

#### **7.7 Adverse Events of Special Interest (AESI) and Reporting Process**

The following adverse events were of special interest in this study: allergic reactions, injection site reactions, transaminase elevations, creatinine elevations, QTc prolongation, gastrointestinal reactions (nausea, vomiting, diarrhea), decreased appetite, dizziness, hypoglycemic events, acute pancreatitis, and severe adverse events of non-serious drug-related adverse events. Investigators should pay close attention to the occurrence of the above adverse events in the clinical study, and timely handle them.

Hypoglycemic events, acute pancreatitis and severe drug-related non-serious adverse events (refer to Section 7.3 of the protocol for severity) should be reported to the sponsor ([contact]; [name]) within 24 hours after awareness, and refer to Appendix 6 for specific procedures.

The above-mentioned Adverse Event of Special Interest (AESI) should be reported according to the SAE reporting process if it meets the criteria of SAE.

##### **7.7.1 Hepatic Function Abnormal Events**

Abnormalities in AST and/or ALT levels accompanied by abnormally elevated total bilirubin levels that meet the conditions in Table 15 and have no other causes of liver injury will be considered as drug-induced liver injury. Such situations should always be considered important medical events.

Table 15. Hepatic Impairment Requiring Reporting as an SAE

| Baseline Period  | Normal (AST/ALT and total bilirubin)                                                                                                           | Abnormal (AST/ALT and total bilirubin)                                                                                                  |
|------------------|------------------------------------------------------------------------------------------------------------------------------------------------|-----------------------------------------------------------------------------------------------------------------------------------------|
| Treatment Period | ALT or AST $\geq 3 \times$ ULN
With total bilirubin $\geq 2 \times$ ULN
And alkaline phosphatase $\leq 2 \times$ ULN
And no hemolysis | AST or ALT $\geq 8 \times$ ULN
Concomitant total bilirubin increase $\geq 1 \times$ ULN or total bilirubin value $\geq 3 \times$ ULN |

Subjects should return to the study site for evaluation as soon as possible (preferably within 48 hours) after learning of an abnormal result. The evaluation should include laboratory tests, detailed medical history and physical assessment, and the possibility of liver neoplasia (primary or secondary) should be considered. In addition to repeat AST and ALT, laboratory tests to be performed should include albumin, creatine kinase, total bilirubin, direct and indirect bilirubin, gamma-glutamyl transferase, prothrombin time/international normalized ratio, and alkaline phosphatase. At the same time, detailed medical history will be collected, including: history of alcohol consumption, acetaminophen, soft drugs, various supplements, traditional Chinese medicine, history of exposure to chemical drugs, family history, occupational exposure, sexual behavior history, travel history, history of contact with subjects with jaundice, surgery, blood transfusion, history of liver disease or allergic disease, history of heart disease, history of immune disease, etc. Further investigations may include tests for acute hepatitis A, B, C, and E, imaging of the liver (e.g., biliary tract), autoantibodies, and cardiac ultrasound. If repeat testing confirms that the laboratory criteria in the table above are met, the possibility of potential drug-induced liver injury should be considered in the absence of other causes of liver function test abnormalities, without waiting for all liver function etiological tests to be made. Such cases of potential drug-induced liver injury should be reported as SAE.

### 7.7. 2 Hypoglycemic Events

According to the classification criteria for hypoglycemia of the American Diabetes Association (ADA)/European Association of Diabetes (EASD) 2017 version, hypoglycemia is defined as follows:

- Warning level (Grade 1) of hypoglycaemia with a plasma glucose concentration of 70 mg/dl or less (3.9 mmol/L):

Symptomatic hypoglycemia: a plasma glucose concentration of less than 70 mg per deciliter (3.9 mmol per liter) accompanied by symptoms associated with hypoglycemia.

Asymptomatic hypoglycemia: a plasma glucose concentration of less than 70 mg per deciliter (3.9 mmol per liter) without symptoms associated with hypoglycemia.

Unclassified hypoglycaemia: plasma glucose concentration no higher than 70 mg per deciliter (3.9 mmol per liter) with no documented information on hypoglycaemic symptoms.

- Clinically significant hypoglycemia (Grade 2) with a plasma glucose concentration of up to 54 mg/dl (3.0 mmol/L):

Symptomatic hypoglycemia: a plasma glucose concentration of less than 54 mg per deciliter (3.0 mmol per liter) accompanied by symptoms associated with hypoglycemia.

Asymptomatic hypoglycaemia: plasma glucose concentration not greater than 54 mg per deciliter (3.0 mmol per liter) without symptoms associated with hypoglycaemia.

Unclassified hypoglycaemia: plasma glucose concentration no higher than 54 mg per deciliter (3.0 mmol per liter) with no documented information on hypoglycaemic symptoms.

- Severe hypoglycemia (Grade 3): Requires assistance of another person to administer carbohydrate, glucagon, or other behavior to aid recovery. During this period, the patient develops a change in state of consciousness, is unable to take care of the aforementioned restorative treatment, is unconscious or semi-unconscious, or becomes comatose (with or without seizure symptoms), and requires intravenous nutrition. During the onset of such symptoms, sometimes the plasma glucose concentration is undetectable at the time of symptom onset, but the symptoms are considered to be directly related to a decrease in blood glucose (plasma glucose concentration not higher than 70 mg per deciliter (3.9 mmol per liter) if neurological symptoms resolve after recovery of the glucose concentration.

Severe hypoglycaemia requiring medical attention: Severe hypoglycaemic events that require treatment by a healthcare provider (e.g., emergency care provider, emergency room staff).

### **Other Hypoglycaemic Events**

- Relative hypoglycaemic events: symptoms associated with hypoglycaemia occur with a plasma glucose concentration above 70 mg per deciliter (3.9 mmol per liter), but it is expected that the plasma glucose level may rapidly approach the threshold of 70 mg per deciliter (3.9 mmol per liter).
- Possible symptomatic hypoglycaemic events: hypoglycaemic symptoms occur without a plasma glucose level measurement, but are thought to be associated with a decrease in the plasma glucose concentration not higher than 70 mg per deciliter (3.9 mmol per liter).

The investigator will determine whether a hypoglycemic event is severe based on the patient's need for medical assistance in addition to the expected assistance that is routinely received by the patient. All hypoglycaemic events will be recorded in the

hypoglycaemic event module of the electronic event report form, and all severe hypoglycaemic events must be reported as serious adverse events.

### **Blood glucose self-monitoring**

During the study, subjects can monitor their fingerstick blood glucose according to their own conditions, and record it in the subject diary. In case of hypoglycemia ( $< 2.8$  mmol/L), they should contact the investigator in time, and instruct to bring the subject diary and blood glucose meter to visit when coming to the hospital.

### **7.7. 3 Gastrointestinal Reactions**

Nausea, vomiting, and diarrhea are the primary gastrointestinal reactions of interest and will be recorded as AE in the eCRF. Each event was assessed for severity, duration (start and stop dates), and relationship to study drug or protocol procedures as deemed by the investigator.

### **7.7. 4 Acute pancreatitis**

Serum amylase and lipase will be monitored at the time points specified in the protocol, and additional tests may be added at the investigator's clinical discretion.

"Blood amylase and/or lipase  $\geq 3$  times ULN, even if the subject does not have symptoms of acute pancreatitis, further diagnostic evaluation is required (refer to Appendix 1)"

## **8 Data Analysis/Statistical Methods**

### **8.1 Statistical Hypothesis**

The primary endpoint of this study is the safety and tolerability of IBI362. No formal statistical tests will be performed.

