### **8.2 Sample Size Estimation**

Five dose cohorts were planned for enrollment. A total of 12 subjects per cohort were planned to be enrolled as 8: 4 to IBI362, placebo-controlled. Approximately 60 subjects in total.

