### **8.4.2 Efficacy Analysis**

All efficacy analyses were performed on the Efficacy Analysis Set. Descriptive statistics will only be performed for efficacy endpoints in this study. For continuous efficacy endpoints, the corresponding mean and two-sided 95% confidence interval will be calculated for IBI362 subjects and all placebo subjects within each dose group, respectively. The p-value for each dose group of IBI362 versus placebo will be calculated using a two-sample t-test and the corresponding point estimate and 95% confidence interval for the difference will be presented. Missing values will be imputed using the LOCF method. The rates within each dose group will be calculated and 95% confidence intervals will be calculated using Clopper-Pearson for the typed efficacy endpoints, and the chi-square test will be used to compare the differences between IBI362 and placebo groups and the corresponding 95% confidence intervals will be calculated. Missing values for typing endpoints will be imputed using the default non-response method.

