#### **8.5 Comparison of multiplicity**

Not applicable.

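### Efficacy analysis is declared descriptive only, yet unlabelled t-test and chi-square p-values are prescribed, and the chi-square condition cannot be met for any single dose group

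*Protocol*

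**What the plan says.** Four places bear on this point.

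- **Protocol 8.4.2 (Efficacy Analysis)** opens with "Descriptive statistics will only be performed for efficacy endpoints in this study". It goes on: "The p-value for each dose group of IBI362 versus placebo will be calculated using a two-sample t-test", with a point estimate and 95% confidence interval for the difference. For categorical endpoints, single-group rates get exact Clopper-Pearson intervals, but for the comparison "the chi-square test will be used to compare the differences between IBI362 and placebo groups". No small-sample alternative is named, and nothing says how the p-values are to be read.
- **Protocol Summary (Statistical Methods)** repeats the same text.
- **Protocol 8.5 (multiplicity)** reads, in full, "Not applicable".
- **Protocol 8.1 (Statistical Hypothesis)** names safety and tolerability as the primary endpoint and then says "No formal statistical tests will be performed".

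On size, 8.2 says "Five dose cohorts were planned for enrollment" and "A total of 12 subjects per cohort were planned to be enrolled as 8: 4 to IBI362, placebo-controlled".

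**The concern.** A plan confined to description has no use for a two-group test, and a plan that does test each of five dose groups cannot call multiplicity inapplicable without explanation. Section 8.4.2 does both within one paragraph. A reader of the eventual report could not tell whether a p-value below 0.05 for one dose group was meant as evidence of effect or as a descriptive aid.

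The categorical test adds a separate problem. Chi-square relies on a large-sample approximation, and each dose group has 8 active subjects. The same sentence uses an exact method for single-group rates, so the small-sample difficulty was recognised for the rates but not for the comparison. At stake is what may be concluded from the efficacy results. Trial conduct and subject safety are unaffected.

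**Working it through.** **Inputs.** Five cohorts, each 8 IBI362 and 4 placebo (8.2). No alpha is stated; two-sided 5% is assumed from the two-sided 95% intervals in 8.4.2. The placebo comparator is not clearly fixed, so both candidates are worked: the 4 placebo subjects of the same cohort, or 5 × 4 = 20 pooled.

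**The plan's own figure.** 5 × (8 + 4) = 60, which matches "Approximately 60 subjects in total". No effect size, SD or power is given, so there is no power statement to reproduce.

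**Multiplicity, one endpoint at one visit.**
- Separate placebo per cohort (independent tests): 1 − 0.95^5 = 0.226, or 22.6%.
- Shared placebo of 20: the tests are correlated. A simulation of 200,000 null trials with Student's t (26 df) gave 20.5%; Welch's version gave 21.7%. Both are about 21%.

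**Chi-square condition.** The smallest expected count in a 2×2 table is (smaller group size × smaller of the responder and non-responder totals) / N. It is largest when the two totals are equal.
- 8 v 4: 4 × 6 / 12 = 2.
- 8 v 20: 8 × 14 / 28 = 4.

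The usual requirement is at least 5 in every cell. No possible response total meets it for a single dose group, with either comparator. Pooling all active subjects (40 v 20) would meet it when total responders lie between 15 and 45, for example 20 × 15 / 60 = 5.

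**True size at nominal 5%.** Found by enumerating every table, with common response rates from 0.05 to 0.95:

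| Comparison | Chi-square, uncorrected (maximum) | Chi-square, continuity-corrected (maximum) | Fisher (maximum) |
|---|---|---|---|
| 8 v 4 | 6.6% (at rate 0.5) | 0.7% | 0.7% |
| 8 v 20 | 4.8% (at rate 0.5) | 1.8% | 3.5% |

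For 8 v 4 the uncorrected size depends on the response rate: 2.4% at 0.1, 5.6% at 0.3 and 6.6% at 0.5.

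**Does the choice of test change conclusions?** Yes, in particular tables. For 8 v 4, eight tables have uncorrected chi-square p ≤ 0.05 but Fisher p > 0.05. One is 5/8 v 0/4: chi-square = 12 × (5×4 − 3×0)² / (8 × 4 × 5 × 7) = 4800/1120 = 4.29, p = 0.038. Fisher gives (56 + 8)/792 = 0.081. For 8 v 20 there are ten such tables, for example 5/8 v 4/20 with 0.030 against 0.068.

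**The case against.** The best defence has five parts.

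1. **Section 8.1 may be narrower than it looks.** Its sentence directly follows the naming of the primary endpoint, so it can be read as saying only that safety is not formally tested. That is a fair reading. A reader might infer that 8.1 bans all testing, but the text does not settle it. The conflict inside 8.4.2 stands either way.

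2. **Without a confirmatory hypothesis, 8.5 is defensible.** This holds if the p-values are understood to be nominal. The protocol does not say they are.

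3. **Chi-square may do little harm.** An expected count of 5 is a rule of thumb, and 8 v 20 shows that breaching it need not inflate error. Section 8.4.1 splits active subjects by dose group but names placebo subjects without that split, which leans towards pooled placebo; 8.4.2 leaves it ambiguous. A continuity correction, about which the protocol is silent, would remove the inflation at 8 v 4. All this stands and limits the size of the point. It does not make chi-square a sound choice, since it still disagrees with the exact test in the tables above.

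4. **The test has no named target.** Sections 2.2.2 and 2.2.3 define no categorical efficacy endpoint. This is correct, and it is a further reason to remove or define the test.

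5. **Details may sit in the SAP.** The interval method for a difference may well do so, and its absence is not counted here. The chi-square test, however, is fixed in the protocol itself.

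Two stronger inferences are tempting. A reader might multiply five groups by every secondary variable and visit and predict a long list of false positives. But 8.4.5 only summarises and analyses those variables by group and does not assign the t-test to each one. A reader might also suppose that the p-values will choose doses. But escalation and the maximum tolerated dose follow safety stopping criteria (2.2.1, 3.2.1), and no decision is tied to an efficacy p-value.

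**Conclusion.** The point holds as an internal contradiction in 8.4.2 and the Summary, together with a poorly chosen categorical test. The p-values are prespecified; the fault is that they are unlabelled and sit under a descriptive-only statement.

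Five unadjusted tests on one endpoint carry about a 21% (shared placebo) to 23% (independent) chance of at least one false positive, assuming two-sided 5%. The usual chi-square condition fails for every per-dose comparison. A reader might infer that the error rate is inflated throughout, but the figures do not show that: inflation, to at most 6.6%, arises only for the uncorrected test with 4 within-cohort placebo subjects. With 20 pooled placebo subjects the maximum is 4.8%. The failure of the condition does not extend to a comparison pooling all IBI362 subjects.

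**What to change.** In 8.4.2 and the Protocol Summary:

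- State that any efficacy p-values are nominal, unadjusted and exploratory, and support no claim of significance. Deleting them would also resolve the conflict, but labelling is enough.
- Replace chi-square with an exact test, Boschloo or Fisher, and report the difference in rates with a Miettinen-Nurminen score or exact interval. Name the categorical endpoint it applies to, or drop the test.
- Say whether the comparator is the 4 placebo subjects of the same cohort or the 20 pooled placebo subjects.

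In 8.5, replace the present entry with a statement that no multiplicity adjustment is made. In 8.1, make clear whether the sentence covers the primary endpoint only.

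The cost is protocol wording. Sample size, visits and conduct do not change. The statistical price is conservatism if Fisher is chosen: its maximum size is 0.7% at 8 v 4 and 3.5% at 8 v 20, so it will rarely reach p ≤ 0.05 against within-cohort placebo. That is a reason to prefer Boschloo or to rely on the interval.
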